#### Surgeon Survey

A modified version of the PROM questionnaire will be distributed to general surgeons (n=10). The general surgeons will be asked to complete the survey only once. The survey will be given to the surgeons with the goal of ascertaining what feedback from patients is most important for them to improve their quality of care. The modified survey will only measure the following factors: (1) procedure perception, (2) hospital perception, and (3) perception of longer-term consequences (see Multimedia Appendix 5).

#### Data Analysis

SPSS v28.0.1.1 (IBM Corp) will be used to complete the data analysis for the patient surveys. The 4-point Likert-scale questions will be tallied into two categories of either “more important” or “less important.” Mean scores will be used to determine the most important and least important factors. Univariate analysis with χ^2^ tests will then be used to determine if any demographic relations exist between what PROs participants find to be more or less important. Additionally, the Wilcoxon ranked sign test and 2-tailed ANOVA will be used to compare the differences between the patients’ answers in their first and second survey responses.

Data from the survey for the surgeons will also be analyzed with SPSS. Mean scores will be tabulated for the general surgeons’ responses to the survey. For the general surgeons’ interviews, the results will be transcribed verbatim and analyzed with thematic synthesis [24]. The qualitative data will explain the overall view that surgeons have regarding PRO collection and the quantitative data will be analyzed in conjunction to illustrate the specific PROs that the surgeons view as important. The patient and surgeon data will also be integrated by comparing the views that both stakeholders have as indicated in the PROM surveys.

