#### Sample Size

This study will aim to recruit 80 patients. This sample size was chosen for the sake of feasibility. Due to time constraints, with 10 months of allocated time for data collection and 2 participating hospitals collaborating on the project, it would not be feasible to collect more data.

Power calculation was considered for determining the sample size. However, power calculation requires an estimation of the proportion of the event of interest [27]. For this study, it would be unrealistic to estimate the number of elective LCs that are completed in Ireland, as these data are not readily available. Consequently, it was decided to estimate the sample size primarily based on feasibility rather than power.

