#### Patient Participant Survey

The survey will be based on the PROM questionnaire, which measures the effect of different factors on the PROs [10]. The following factors will be measured using the PROM survey: (1) age, sex, education level, marital status, employment status, ethnicity, smoking, and exercise frequency; (2) procedure perception; (3) hospital experience perception (PREMs); and (4) perception of longer-term consequences.

In addition, the acceptability and perceived value of the PROMs will be assessed with a survey from Stover et al [28].

The presurvey will be administered electronically by email using Qualtrics to patients who have completed an elective LC within the past 48 hours. These patients will then be followed up after 1 year and the survey will be administered again (Multimedia Appendix 2).

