## Discussion

### Study Significance and Strengths

This study will convey the perspective of participants regarding which PROs are most important for them after LCs. Based on prior research, we expect the technical skill and experience level of the surgeon, long-term quality of life, patient involvement in decision-making, communication skills of the surgeon, cleanliness of the ward environment, and standards of nursing care to be the most important factors for the patients [10]. Furthermore, this study will indicate the acceptability and perceived value of participants regarding electronic PRO surveys, which is a topic that is relatively more limited in the literature in the context of LCs. The study has well-defined inclusion and exclusion criteria, with all patients being given the survey less than 48 hours after their surgery and only elective cases being included. This will help make the sample more homogenous, as patients undergoing emergency surgery might have different perspectives on what is important for them in comparison to those having elective surgery [11].

Furthermore, the long-term follow-up of 1 year will assist in better understanding the views of patients undergoing LC. The distribution of the survey to postoperative patients will ensure that the patients already had the experience of having an LC and can reflect upon it when answering the survey. This perspective would not be achievable with patients in a preoperative setting. The use of a 50-item survey also ensures that several PROs and factors will be analyzed, thereby offering a broad view of patients’ perspectives on PROs. Moreover, the integration of the perspectives of surgeons regarding the study may help elucidate improved procedures when following up with patients.

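### Testing demographic relations by chi-square on four-level items cut to two categories discards ordering and costs power that a sample of 80 can ill spare

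*Protocol article*

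**What the plan says.** In the protocol article, Data Analysis fixes both the coding and the test for the demographic question. "The 4-point Likert-scale questions will be tallied into two categories", more important and less important, and univariate chi-square "tests will then be used to determine if any demographic relations exist between what PROs participants find to be more or less important". The cut-point between the two categories is not given.

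The same section ranks factors by mean score and compares the first and second surveys with a Wilcoxon test and ANOVA. Neither is stated to use the two-category coding, so the collapse is tied explicitly only to the demographic analysis.

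Patient Participant Survey lists the demographics as "age, sex, education level, marital status, employment status, ethnicity, smoking, and exercise frequency". Under Sample Size, "This study will aim to recruit 80 patients", and the basis is feasibility: "Consequently, it was decided to estimate the sample size primarily based on feasibility rather than power". Limitations then offers the demographic analysis as mitigation for the bias of convenience sampling.

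**The concern.** A four-level importance score is ordered. Reducing it to two categories treats the two levels within each half as identical, so a group that mostly picks the top level looks the same as one that mostly picks the level below it. Chi-square also takes no account of order in demographics that are naturally ordered, such as education or exercise frequency, if these are recorded in ordered categories.

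The sample is fixed by feasibility and cannot easily be enlarged, so information already collected should not be thrown away. Limitations leans on this analysis when it discusses sampling bias, and an insensitive test that finds nothing could give false reassurance there.

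**Working it through.** **Inputs from the article:** N = 80; four ordered levels reduced to two; chi-square test; eight demographic variables. No power, alpha or effect size is given, so there is no planned power figure to reproduce.

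**Assumptions, none of them in the article:** two-sided alpha 0.05; groups of 40/40 or 60/20; the response distributions below; a cut between levels 2 and 3 unless stated otherwise; a proportional-odds shift, in which one group's cumulative odds are multiplied by 3.

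**Step 1. What the shift means.** New share p' = 3o/(1 + 3o), where o = p/(1 − p).
- 2/8/35/55% item: low share 10%, o = 0.111, 3o = 0.333, p' = 25%. Low answers with 40/40 groups: 40 × 0.10 + 40 × 0.25 = 14, an expected count of 7 per group.
- 5/15/40/40% item: low share 20%, o = 0.25, 3o = 0.75, p' = 42.9%. Low answers: 8 + 17.1 = about 25, an expected count of about 12.6 per group.
- 20/30/30/20% item: low share 50%, o = 1, 3o = 3, p' = 75%. Low answers: 20 + 30 = 50, leaving 30 high answers, an expected count of 15 per group.

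**Step 2. Power by simulation:** uncorrected chi-square on the two categories against Mann-Whitney on four levels, odds ratio 3.

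| Item (levels 1 to 4) | 40/40: chi-square | 40/40: Mann-Whitney | 60/20: chi-square | 60/20: Mann-Whitney |
|---|---|---|---|---|
| 2/8/35/55% | 43% | 72% | 39% | 63% |
| 5/15/40/40% | 59% | 75% | 54% | 64% |
| 20/30/30/20% | 64% | 75% | 51% | 63% |

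The losses at 40/40 are 29, 16 and 11 points. With no true difference, Mann-Whitney rejected in about 4% to 6% of runs, so its advantage does not come from an inflated error rate. Fisher's exact test on the collapsed 2/8/35/55% item reaches only about 33%.

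**Step 3. Dependence on the cut-point.** If only the top level counts as more important, the 2/8/35/55% item at 40/40 gives 67% against 72%, a loss of about 5 points. The 5/15/40/40% item still gives about 60% against 75%.

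**Step 4. When cells become sparse.** Expected count in the smallest group = group size × overall less-important share. Setting this to 5:
- 40/40: 5/40 = 12.5%
- 60/20, or four equal categories of 20: 5/20 = 25%
- five equal categories of 16: 5/16 = 31.25%

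Below these shares the usual condition fails. The three 40/40 scenarios in Step 2 are above the 12.5% threshold, so their power loss comes from lost ordering and not from sparse cells. The 60/20 case of the first item is sparse: (60 × 0.10 + 20 × 0.25) × 20/80 = 2.75.

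**Step 5. What remains after the change.** At odds ratio 2 with 40/40 groups, the rank test has about 36% to 40% power and chi-square 12% to 34%, for low shares from 5% to 50%. Even for a balanced item, chi-square for 50% against 70% has only about 45%.

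**The case against.** A reader might infer that the collapse will certainly leave too few less-important answers. The article does not support this. It gives no response distribution and no cut-point. Study Significance and Strengths expects items such as "communication skills of the surgeon, cleanliness of the ward environment, and standards of nursing care to be the most important factors", but that predicts a ranking and not the share of answers in the upper levels. The Introduction also names factors found relatively less important in earlier work, so a ceiling across the whole survey cannot be assumed. Sparse cells are therefore only a conditional risk.

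The power comparison also favours the rank test, because a proportional-odds shift is the pattern that suits it. If groups differ only in crossing the important/unimportant line (10% against 25% low, with the same top-level share), chi-square wins by about 43% to 9%. That binary contrast is close to the question as Data Analysis words it. This objection stands, and it is why the two-category comparison should be kept.

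Demographic relations are not among the study objectives, the article calls this a feasibility study, and the sample size is a main limit under either test. No passage says that a null result will be taken as no relation. These points lower the stakes. They do not make the choice an omission that a fuller plan would fill, because the article itself states the coding and the test.

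**Conclusion.** The point holds in a limited form. The stated demographic analysis gives up ordinal information and, for a shift across the whole scale, lost power under every response distribution, group split and cut-point tried. With odds ratio 3, N = 80 and 40/40 groups, the loss runs from about 5 to 29 points, depending on the assumed item distribution and cut-point. Expected counts below 5 are an added problem only below the shares in Step 4, and whether they occur cannot be told from the article. The conclusion concerns the demographic analysis alone. It does not reach the factor ranking, the comparison of the two surveys or the study objectives. Keeping the four levels recovers power but does not make 80 patients adequate for modest differences.

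**What to change.** In Data Analysis, make the main demographic tests use the four original levels: Mann-Whitney for two groups, Kruskal-Wallis for unordered groups, and Spearman or a linear-by-linear trend test for ordered demographics. Keep the two-category tally, with its cut-point stated, as a descriptive or secondary comparison. Switching only to Fisher's exact test on the tally would deal with small expected counts but lose further power.

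Add that these analyses are exploratory and that a null result is not evidence of no demographic relation, and carry this into Limitations where the analysis is offered as mitigation.

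The cost is wording only: no new data are needed and the tests are standard in SPSS. The downside is lower sensitivity of the rank test when groups differ only across the important/unimportant line, which the retained secondary comparison covers.

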### Limitations

As a result of this being a feasibility study, there are several associated limitations. Primarily, the small sample size of 80 participants will limit the generalizability of the study. Moreover, the use of convenience sampling also limits the external validity and generalizability of the results. It has been shown that convenience sampling has greater validity when the sample is more homogenous with respect to the participants’ sociodemographic characteristics [31]. However, making the sample completely homogenous in this study would result in an inadequate sample size. Thus, this bias will be mitigated through statistical analyses exploring differences in the factors that are deemed important according to the participants’ demographic characteristics. Another significant bias associated with using convenience sampling is that the participants accepting to partake in the study could be more likely to find perceived value in completing the electronic survey in comparison to those who declined to participate. These biases will be mitigated through the use of rigid inclusion and exclusion criteria, ensuring that the sample is as homogenous as possible.

Another limitation is the use of a 4-point Likert scale. Likert scales ideally have between 4 and 7 options, although 4-point scales might commit participants to give answers they may not wish to give [32].

Although only including patients undergoing elective surgery will aid in further defining the inclusion and exclusion criteria, this restriction will also limit the generalizability of this study, as patients undergoing emergency LC will not be represented.

In addition, recruiting patients within 48 hours of their LC means that their postoperative condition could influence their answers. The survey also contains mild medical jargon (eg, “bile leak”) that might be confusing for participants.

There is no electronic literacy scale for the participants involved. Incorporation of such a scale would have improved the interpretation of the results by demonstrating whether the ability to use technology impacts the participants’ views on electronic surveys.

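### Raw mean scores decide which factors matter most, and patients are compared with surgeons, with no stated allowance for imprecision at close ranks or for only 10 surgeons

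*Protocol article*

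**What the plan says.** In Data Analysis, the patient ratings are first collapsed: "The 4-point Likert-scale questions will be tallied into two categories of either" more or less important. The next sentence gives the ranking rule: "Mean scores will be used to determine the most important and least important factors". The article does not say whether the mean is of the 4-point or the collapsed score; the 4-point score is assumed below. The same section names χ² tests for demographic relations, and a Wilcoxon test and ANOVA for first versus second survey. For surgeons it says that mean scores will be tabulated and that the two groups' views will be compared.

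Study Significance and Strengths makes the ordering an output of the study: "This study will convey the perspective of participants regarding which PROs are most important for them after LCs". It lists six factors expected to lead, beginning "we expect the technical skill and experience level of the surgeon, long-term quality of life, patient involvement in decision-making". It also says: "The use of a 50-item survey also ensures that several PROs and factors will be analyzed". Conclusions adds that the results will show where surgeons and patients differ.

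On size, the Sample Size section says "This study will aim to recruit 80 patients" and that "it was decided to estimate the sample size primarily based on feasibility rather than power". Ten surgeons will complete a modified version of the questionnaire.

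**The concern.** The ranking rule uses point estimates alone. When many items are rated on a short scale, neighbouring true means must lie close together, and their observed order is then partly chance. Any list of the most important factors has an edge, and items near it can fall on either side.

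The patient-surgeon comparison is more exposed, because a mean over 10 people is far less precise than a mean over 80. If two raw orderings are set side by side, they will differ even when the two groups think alike. What is at stake is a reported difference between stakeholders, or a reported departure from the six expected factors, that is only sampling error.

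**Working it through.** The article states no precision, power or effect size for the ranking, so there is no figure of its own to reproduce.

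**Inputs from the article.** 80 patients; 10 surgeons; a 4-point scale; 50 survey items; six expected factors.

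**Assumed inputs.** The number of ranked items (30 or 40, since some of the 50 are demographic or acceptability questions), the item SD (0.5 to 0.9), the correlation between two items in the same patient (0 to 0.6), and the spread of true item means.

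**Step 1: one item mean, n=80.** Half-width = 1.96 × SD/√80. This gives 0.11, 0.15 and 0.20 points for SD 0.5, 0.7 and 0.9.

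**Step 2: two items in the same 80 patients.** Half-width = 1.96 × SD × √(2(1−ρ)/80).
- SD 0.5, ρ 0.6: 1.96 × 0.5 × √0.01 = 0.10
- SD 0.7, ρ 0.3: 1.96 × 0.7 × √0.0175 = 0.18
- SD 0.9, ρ 0: 1.96 × 0.9 × √0.025 = 0.28

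For comparison, a scale from 1 to 4 is 3 points wide. If K items filled all of it, the average gap between neighbours would be 3/(K−1): 3/29 = 0.10 for 30 items and 3/39 = 0.08 for 40. That extreme spread only just matches the smallest half-width. Any realistic spread gives smaller gaps, so typical neighbours cannot be separated.

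**Step 3: how much of the order survives at n=80.** This is a simulation with 1,000 runs per setting. Latent item means are centred on 3.2, the latent SD is 0.8, the within-person correlation is 0.3, and scores are rounded and clipped to 1–4. Each range covers 30 and 40 items.

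| SD of true item means (observed scale) | Rank correlation with truth | True top six recovered (mean) | Exact top six | True top item ranked first |
|---|---|---|---|---|
| 0.13 | 0.84 | 3.9–4.2 | 3–6% | 47% |
| 0.25 | 0.94–0.95 | 4.8–4.9 | 17–18% | 68% |
| 0.40 | 0.98 | 5.2–5.3 | 32–39% | 74–78% |

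The broad order is fairly stable; exact positions and the edge of a top list are not.

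**Step 4: surgeons, n=10.** Half-width for one item mean = 1.96 × SD/√10, which is 0.31, 0.43 and 0.56 points for SD 0.5, 0.7 and 0.9 (a t quantile would widen these). In the same simulation the rank correlation with truth falls to 0.49–0.88, and the true top item is ranked first in 14–45% of runs.

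**Step 5: patients against surgeons with identical true means.** Under the Step 3 assumptions, the two observed top-six lists share on average 2.1 to 4.2 items. They match exactly in about 0–5% of runs.

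**Step 6: the same comparison item by item.** Half-width for a difference in means = 1.96 × SD × √(1/80 + 1/10) = 1.96 × SD × 0.335. This is 0.33, 0.46 and 0.59 points for SD 0.5, 0.7 and 0.9. It is wide, but it shows the reader how little 10 surgeons can exclude.

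**The case against.** The best reply is that this is a descriptive feasibility study reported in a condensed article. Its two listed objectives, acceptability and perceived value of electronic PROs and feasibility of email follow-up, do not turn on exact ranks. Confidence intervals beside a mean are often left to a fuller document. Item count, SD and spread are all assumed here, and exact recovery of a top six is a criterion that the article never sets. Limitations also concedes that "the small sample size of 80 participants will limit the generalizability of the study".

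Much of this stands, and it keeps the point small. It does not remove it. The article does more than omit an interval: it says that the means determine the most and least important factors, while it names tests for the other comparisons in the same section. Other Data Collection Tools Considered gives learning what patients find most important as the reason for choosing this survey. The admitted limitation concerns generalizability, not the precision of the order.

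A reader might infer three stronger claims, and the documents support none of them:
- **That the patient ranking is largely unstable.** Step 3 shows the broad order mostly recovered, and the size depends on inputs not given.
- **That the ranking will be presented as certain.** No section says so; the article only leaves uncertainty unmentioned for this step.
- **That the 12-month comparison rests on the ranking.** Data Analysis tests patients' first and second answers directly, not two rank lists.

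**Conclusion.** The point holds in a limited form. A rule based on raw means can support a broad description of higher- and lower-rated factors with 80 patients. It cannot support a strict order among close items, a firm edge to a most-important list, or a claim that surgeons and patients differ because their orderings differ.

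The half-widths rest on the assumed SD and correlation ranges. The top-six figures rest further on the assumed item count, spread and scale behaviour, so they illustrate the problem and do not predict this study's result. The direction for the patient-surgeon comparison was the same in every setting tried: identical views gave visibly different top lists. This is a worthwhile, inexpensive improvement and not a flaw that undermines the study.

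**What to change.** In Data Analysis:
- State which score the mean uses (4-point or collapsed). Report each item's mean with a 95% confidence interval and a bootstrap interval for its rank, resampling whole respondents so that the correlation between items is kept.
- Describe items whose rank intervals overlap as tiers and not as a strict order. Judge the six expected factors by the tier in which each falls. No pass mark requiring a rank interval to lie inside a fixed top group is needed; with 80 patients such a rule could exclude items that truly belong there.
- For patients against surgeons, report the difference in means with a 95% confidence interval for each item that both groups answer, and draw no conclusion from differences in rank order alone.

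The cost is a few sentences in the plan and a little more analysis. No new data are needed. The ranking will look less clear-cut, and many patient-surgeon differences will be inconclusive with 10 surgeons.

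### The chi-squared tests planned for all demographics ignore the order of age, education level and exercise frequency, and are unreliable where a demographic group is very small

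*Protocol article*

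**What the plan says.** The protocol article's Data Analysis section first reduces the item scale: "The 4-point Likert-scale questions will be tallied into two categories of either" more or less important. Univariate chi-squared "tests will then be used to determine if any demographic relations exist between what PROs participants find to be more or less important".

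The demographics come from the Patient Participant Survey section: "age, sex, education level, marital status, employment status, ethnicity, smoking, and exercise frequency". Age, education level and exercise frequency have a natural order. The others are binary, unordered or of unclear form. All eight receive the same test, and no trend or exact method is named.

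The Sample Size section gives the number of patients, "This study will aim to recruit 80 patients", and its basis: "it was decided to estimate the sample size primarily based on feasibility rather than power". No significance level, power or effect size appears in the article. The number of categories per demographic is in a survey appendix that is not shown.

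The Limitations section gives these comparisons a role. On convenience sampling it says that "this bias will be mitigated through statistical analyses exploring differences in the factors" rated important, by demographic characteristics.

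**The concern.** The natural question for an ordered demographic is whether importance rises or falls along it. Pearson chi-squared does not ask that. Its value stays the same if the age bands are shuffled, and it spreads a gradient over k − 1 degrees of freedom, where k is the number of groups. A trend test puts the same signal on one degree of freedom. With 80 patients and a size set by feasibility, there is little power to give away.

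Unordered factors raise a different problem. If some groups hold only one to three patients, the chi-squared approximation breaks down and the p-value no longer means what it says.

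What is at stake is how a null result will be read. Because the Limitations section relies on these comparisons to deal with sampling bias, a missed gradient could be taken as reassurance that demographics do not matter, and a spurious result from one or two patients could be taken as a finding.

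**Working it through.** **Inputs from the protocol.** n = 80 (Sample Size); binary outcome and chi-squared tests (Data Analysis); three ordered demographics among eight (Patient Participant Survey). The sample size has no formula behind it, so there is no planned figure to reproduce.

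**Assumptions not in the protocol.** Two-sided 5% level; k equal (or as near equal as 80 allows) ordered groups; log-odds of 'less important' rising evenly from the first group to the last; 20–40% 'less important' overall.

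**Formula.** For a k × 2 table, the Pearson noncentrality is λ = Σ nᵢ(pᵢ − p̄)² / [p̄(1 − p̄)] on k − 1 degrees of freedom. The trend noncentrality is λ_T = [Σ nᵢsᵢ(pᵢ − p̄)]² / [p̄(1 − p̄) Σ nᵢ(sᵢ − s̄)²] on 1 degree of freedom, with equally spaced scores sᵢ.

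**Worked case: k = 4, 20 per group, odds ratio 6, average 30%.**
- Group proportions are 13.8%, 22.6%, 34.6% and 49.0%. Check: (0.490/0.510) / (0.138/0.862) = 6.0.
- Squared deviations from 0.30 sum to 0.0262 + 0.0055 + 0.0021 + 0.0362 = 0.0700, so λ = 20 × 0.0700 / 0.21 = 6.67.
- With scores −1.5, −0.5, 0.5 and 1.5, Σ sᵢpᵢ = 1.5 × (0.4902 − 0.1381) + 0.5 × (0.3461 − 0.2256) = 0.588. Then λ_T = (20 × 0.588)² / (0.21 × 20 × 5) = 6.6. Almost the whole signal lies in the trend.
- The critical values are 7.81 on 3 degrees of freedom and 3.84 on 1. Power is about 57% for Pearson and 73% for trend. Simulation gives 57% and 75%.

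**Simulated power (40,000 runs per setting), range over 20–40% 'less important'.**

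| Odds ratio, end groups | k | Pearson | Trend |
|---|---|---|---|
| 6 | 3 | 59–79% | 70–87% |
| 6 | 4 | 43–65% | 62–81% |
| 6 | 6 | 30–47% | 55–74% |
| 3 | 4–6 | 13–28% | 26–42% |

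With two groups there is no difference (84% for both at odds ratio 6 and 20% 'less important'). With no association, both tests reject in about 5% of runs (4.4–5.2%).

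**A different gradient.** With 'more important' rising in a straight line from 40% to 80%, power is 63% v 79% at k = 4 and 44% v 72% at k = 6. The conclusion is the same.

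**Non-monotone pattern.** For 60/20/20/60% in four equal groups, Pearson has 90% power and the trend test 5%.

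**Sparse groups.** The split 74/3/2/1 is illustrative. Take 10% 'less important'. If the single patient in the smallest group gives that answer, that row contributes about (1 − 0.1)²/0.1 + (0 − 0.9)²/0.9 = 8.1 + 0.9 = 9.0, which already exceeds the critical value of 7.81. One answer decides the test. At 30% the same row contributes only (0.7)²/0.3 + (0.7)²/0.7 = 1.6 + 0.7 = 2.3. Simulated type I error of Pearson, against a nominal 5%:

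| 'Less important' | 5–10% | 20% | 30–40% |
|---|---|---|---|
| Actual type I error | 11–12% | about 6% | 1–3% |

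**The case against.** **A journal article condenses the plan, and details of a chi-squared test belong elsewhere.** Partly right. A missing small-cell rule alone would not be a point. The linear-by-linear test is also a 1-df chi-squared test, so the wording does not strictly exclude it. But the article does state a method, and it gives that one method to ordered and unordered variables alike. Pearson is the natural reading.

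**The gain rests on assumed category counts and a very large effect.** This stands as a limit on size. At three groups the gain is about 8–11 points, and with two it is nil. A reader might infer that a trend test would recover most real gradients. It would not: at an odds ratio of 3 it has only 26–42% power. That shortfall comes from the sample size, and the article openly admits that the sample is small.

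**The type I error figure depends on the split.** This also stands. Groups of 72/8 or 40/25/10/5 give 4–5.3%. The inflation and the power figures also apply to different kinds of item: the error is inflated when few answer 'less important', whereas the power figures assume 20–40%. A reader might infer that a stated 5% level is breached, but the article states no level. Nor is the distortion always inflation, since it turns conservative when 'less important' is common.

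**The general test suits an open question.** The plan asks whether any relation exists and predicts no direction. A reader might conclude that the trend test should replace chi-squared. The U-shape result shows what that would lose, so the general test should stay.

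**Banding age is not shown to be a fault.** Correct. How age is recorded is not visible, and the survey may already collect bands.

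**Conclusion.** The point holds in limited form. The stated method is inefficient for three of the eight demographics if they have three or more categories and the relation is monotone. It is unreliable for any demographic with very small groups. For a strong gradient (odds ratio 6), the loss against a trend test is modest at three groups and roughly 16–28 points at four to six. For a moderate gradient (odds ratio 3), the trend test does better but still misses most. With sparse groups, the actual error rate can be more than double the nominal level or well below it.

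These sizes rest on an assumed 5% level, equal groups, assumed category counts and an illustrative sparse split. The direction of the first result does not depend on the exact settings, provided that there are at least three groups and the gradient is monotone. The documents do not support a claim that the study's main aims are compromised: acceptability, perceived value and feasibility of email follow-up do not depend on these tests. The change is still worth making, because the Limitations section relies on these comparisons and a better method uses the same tables.

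**What to change.** In Data Analysis, replace the single chi-squared statement with three:

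1. For age, education level and exercise frequency, the main test is the linear-by-linear (trend) association, or a rank-based comparison using age in years if age is recorded that way.
2. For the same three factors, the general chi-squared test is kept as a secondary check for non-monotone patterns.
3. For the unordered factors, the Fisher-Freeman-Halton exact test is used when expected counts are small, for example below 5.

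State the significance level used. It would also help to say in Limitations that, with 80 patients, a non-significant result does not show that a demographic is unrelated to importance.

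The cost is a few sentences and one additional exploratory test per ordered factor. No further patients or data are needed. The trend test has little power for U-shaped patterns, which is why the general test stays.
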